## Abstract

**Background:**

Due to ongoing rise in need for care for people with chronic diseases and lagging increase in number of care providers, alternative forms of care provision and self-management support are needed. Empowering patients through an online care platform could help to improve patients’ self-management and reduce the burden on the healthcare system.

**Methods:**

Access to laboratory results and educational modules on diabetes will be offered through a platform for subjects with type 2 diabetes mellitus treated in primary care. Differences in socio-demographic and clinical characteristics between subjects expressing interest vs. disinterest to use the platform will be explored. Platform usage will be tracked and compared. Patient satisfaction and quality of life will be measured by validated questionnaires and economic analyses will be performed.

**Discussion:**

This study is designed to assess the feasibility of use of an online platform in routine primary healthcare for subjects with type 2 diabetes mellitus in the Netherlands, and to study effects of use of the platform on treatment satisfaction, quality of life and clinical parameters. Although providing access to a online platform is not a novel intervention, usage and effects have not yet been studied in this patient population.

**Trial registration:**

Trial registration: NCT01570140.

## Background

Worldwide a dramatic increase is seen in the prevalence of diabetes. In 2007, the prevalence of diabetes in The Netherlands was estimated to be 740,000, while in a conservative estimate this is expected to rise to over 1,300,000 in 2025, of which more than 90% will have type 2 diabetes mellitus (T2DM) [1,2]. At the same time, the increase in number of care providers is lagging. This inevitably will result in an actual decrease in available face-to-face time for contacts between patients and care providers. This necessitates development of alternative forms of treatment and support of patients’ needs and self-management abilities beyond current situation and possibilities [2].

One possibility for reducing workload is increasing patients’ participation in their own care by promoting knowledge regarding their chronic disease(s) and insights in their own situation. Improving online access to reliable information through promoting use of an online platform may help to support such goals [3], but may also result in reducing workload for caregivers. Furthermore, by creating patient profiles, more specifically tailored educational and training can be offered. Personal contact through internet between patients and care providers will also add value. Access to credible health information and personal health data may potentially lead to better disease management and improvement of health. Also, collaborative disease tracking may decrease communication barriers between patients and caregivers. This may lead, in turn, to better understanding, more self reliance and promoting taking responsibility [3], with hopefully and eventually lower costs.

Large programs have been started and results have been analysed in the past decades (resulting in decidedly mixed results), such as the Whole System Demonstrator (WSD), to study effects of telehealth and telecare [4] and a study by Kennedy et al. on implementation of self-management support [5]. However, to see some of the positive study results translated into (cost) effective use of e-Health in routine general practice seems to be quite a challenge up to now [6]. In an effort to further explore opportunities and barriers, the current study aims to provide data access and education through an interactive care platform to T2DM patients in primary care in The Netherlands.

The use of this care platform will be offered as part of the e-Vita research program, in which a care platform will be implemented and studies in various regions of The Netherlands. Six sub-studies will be performed, three of which are in patients with different chronic illnesses: T2DM, chronic obstructive pulmonary disease (COPD) and/or chronic heart failure (CHF). The fourth study concentrates on cost-effectiveness of these interventions and will be performed by the Julius Center in Utrecht. The fifth study will assess determinants of platform usage, by using methods developed by the Center for eHealth Research and Disease Management, Department of Psychology, Health and Technology, University of Twente, Enschede. The sixth study is part of the study in T2DM patients and is performed by the Department of Medical Psychology, VU University Medical Center, Amsterdam.

The presented study is performed in T2DM patients in the Netherlands, treated in primary care. Patient empowerment is strived for by offering the possibility to track laboratory results based on the yearly check-ups, as well as offering educational modules to start a self-chosen process of lifestyle intervention through the platform. Even small improvements in lifestyle may on longer term result in moderate to large changes in self-reported dietary and physical activity behaviours that can result in (cost-effective) improvements in health related measurements (adiposity, blood pressure and lipid levels) [7,8]. Other results may be improvements in patients’ health related quality of life (HRQoL) [9], which in itself is an independent predictor of mortality in patients with T2DM [10,11]. The earlier mentioned study performed by the VU University Medical Center is a randomized controlled trial nested within the T2DM study, comparing effects of online coaching vs. no coaching of a self-management support module on self-reliance [12].

### Objectives e-VitaDM

This study will investigate the hypothesis that use of a care platform and its educational content by T2DM patients will positively influence perceived quality of life, wellbeing and degree of self-reliance [13-16]. Also, patients’ opinion regarding received care will be assessed [17,18]. Furthermore, the influence of platform use on clinical parameters, like glycaemic control, will be investigated. Besides direct benefits for patients themselves, e-health facilities could result in reduction of medical care utilization, less workload for care providers and decrease of costs of care.

### Objectives ZODIAC

All patients in the study will also be assessed in a long-term follow-up study for at least the next ten years. This prospective observational study should be considered the continuation of the Zwolle Outpatient Diabetes Project Integrating Available Care (ZODIAC) started in 1997 [19-25]. It will assess the effects of clinical parameters and quality of life on micro- and macrovascular complications and mortality. In addition, it will address relevant questions in relation to present routine of diabetes care by adding more up-to-date data in comparison with the initial phase of the ZODIAC project.

## Methods

### Study design

A prospective observational study of patients volunteering to use the interactive care platform (e-VitaDM), within the ZODIAC study (see Figure 1). Nested in this observational study a randomized controlled trial is planned testing coaching vs. non-coaching of a self-management support module (see Figure 2) [12].

**Figure 1 F1:**
[figure not shown]
Patient flow.

**Figure 2 F2:**
[figure not shown]
RCT nested in e-VitaDM study.

### Study population

The included sample consists of patients with T2DM treated in primary health care in the Drenthe-region of The Netherlands as part of the shared care initiative of the Care Group Drenthe (CGD). Some specific inclusion- and exclusion criteria have been formulated:

#### Inclusion criteria

Patients can participate when they are diagnosed with T2DM (ICPC T90.2), with the GP defined as main care provider, when they are part of the Drenthe shared care initiative, and when they are aged ≥18 years.

#### Exclusion criteria

There are no exclusion criteria for the cohort study (ZODIAC). For the intervention study (e-VitaDM) exclusion criteria are:

Not participating in the shared care initiative

Mental retardation or psychiatric treatment for schizophrenia, organic mental disorder or bipolar disorder currently or in the past

Insufficient knowledge of Dutch language to understand the requirements of the study and/or the questions posed in the questionnaires

Life expectancy <1 year due to malignancies or other terminal illnesses

Cognitive impairment, including dementia, that interferes with trial participation

Any condition that the investigator of coordinating investigator feels would interfere with trial participation or evaluation of results

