### Measurements

Table 1 shows an overview and time schedule for data to be collected in the intervention study (e-VitaDM) and the observational cohort study (ZODIAC). The collection of data follows NEN-procedure 7510 and all substandards based on the ISO 27000 series. In addition, all identifiable personal information will be encrypted in accordance with the Rijndael algorithm.

**Table 1 T1:** Overview and time schedule for data to be collected

	**Patients using platform (e-VitaDM)**				**Patients in cohort only (ZODIAC)**			
	**T-1**	**T0**	**T1**	**T2**	**T-1**	**T0**	**T1**	**T2**
Patient profile		X				X		
Use of platform			X	X				
EQ-5D, EQ-VAS, WHO-5, PAID-5,		X	X	X		X	X	X
SDSCA	X			X	X			X
Europep								
Laboratory/clinical measures		X		X		X		X
Medication care utilization		X	X	X		X	X	X
Micro- and macrovascular complications		X		X		X		X
Mortality, assessed by PN/GP				X				X
Number of encounters with care providers				X				X
Mortality, CBS, GBA				X				X

The baseline assumption is that ≥90% will participate in the long-term study (ZODIAC), as was our experience in the earlier ZODIAC-study, but that no more than 20% of the patients will express interest in the e-Vita platform (e-VitaDM).

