#### Quality assessment lists

All patients with T2DM participating in the observational cohort study (including those who are not interested in the platform) are asked to fill in a range of validated questionnaires to measure perceived quality of life (EQ-5D) [13], well-being (WHO-5) [14], diabetes-distress (PAID-5) [15], diabetes self-care behaviour (SDSCA) [16] and perceived quality of received care (Europep) [17,18]. Additional questions about coffee/tea intake, smoking habits, employment and educational background are included as well. Questionnaires are filled in at different time points (see Figure 3).

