### Statistical analyses

#### Analyses in intervention study (e-VitaDM)

To evaluate differences in target variables over time and within groups, we will use the linear mixed model for repeated measures. Variables measured after 6 and after 12 months will be used as within-subjects variables. Baseline variables will be used as covariates. Making use of the platform or not will be used as a between-subjects factor. In case of differences between groups on relevant variables, these variables will be added as a covariate in the multivariable analyses.

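### The e-VitaDM exclusion criteria apply only to the platform group, so the natural EQ-5D comparator, the cohort-only patients, can include people who could never have been platform users

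*Protocol article*

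**What the plan says.** The Exclusion criteria section treats the two studies differently. For the cohort: "There are no exclusion criteria for the cohort study (ZODIAC"). Then: "For the intervention study (e-VitaDM) exclusion criteria are", followed by six items. One concerns mental health: "Mental retardation or psychiatric treatment for schizophrenia, organic mental disorder or bipolar disorder currently or in the past". Another concerns language: "Insufficient knowledge of Dutch language to understand the requirements of the study and/or the questions posed in the questionnaires". A third concerns prognosis: "Life expectancy <1 year due to malignancies or other terminal illnesses". The others are cognitive impairment that hampers participation, an open-ended investigator judgement, and not being in the shared care initiative. The last does not separate the groups, because the Inclusion criteria already require shared care of everyone. Five criteria therefore apply to one side only.

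Under Setting, every patient who meets the inclusion criteria is invited to ZODIAC, and those who express interest are registered on the platform and enter e-VitaDM. Table 1 (Measurements) sets the platform patients beside a column headed "Patients in cohort only (ZODIAC"), with EQ-5D at T0, T1 and T2 in both. Quality assessment lists confirms this: "All patients with T2DM participating in the observational cohort study (including those who are not interested in the platform) are asked to fill in" the questionnaires. Under Analyses in intervention study (e-VitaDM), the contrast is defined as follows: "Making use of the platform or not will be used as a between-subjects factor". Baseline variables are covariates, and relevant variables that differ between groups are added. EQ-5D is the primary outcome, with 0.074 as the predefined relevant difference. Nothing in the article limits the non-users to patients who could have joined e-VitaDM.

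**The concern.** Self-selection of volunteers is inherent in this observational design, and the article is open about it. This difference is of another kind: it is written into the eligibility rules and can be removed. A patient not expected to live a year may be a comparator but never a user, while the outcome is measured at 6 and 12 months. A patient whose Dutch is too poor for the questionnaires is kept out of e-VitaDM, yet no rule keeps that patient's answers out of the comparator.

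At stake is the primary comparison. If the ineligible patients who do contribute data lose quality of life faster than their baseline score predicts, the platform group looks better with no platform effect at all. With thousands of comparators, even a small systematic shift can be declared statistically significant.

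**Working it through.** The article states no sample size, SD or power, so there is no figure of its own to reproduce.

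**1. Do the groups overlap on the excluded characteristics?**

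| | Platform (e-VitaDM) | Cohort only (ZODIAC) |
|---|---|---|
| Life expectancy below 1 year | barred | allowed |
| Cognitive impairment hampering participation | barred | allowed |
| Listed psychiatric illness, mental retardation | barred | allowed |
| Insufficient Dutch | barred | allowed |
| Investigator judgement | barred | not applied |
| Not in shared care | barred | barred by the inclusion criteria |

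In the first five rows there is no overlap by rule. The data then hold nothing on how such patients fare as users, and the model can only extrapolate. Baseline EQ-5D adjusts for the starting level, not for a steeper later decline. An indicator for ineligibility would work only by setting these patients aside, which is restriction under another name. It would also need eligibility to be recorded in cohort-only patients, which the article does not describe.

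**2. Approximate group sizes.** From Setting and Measurements: about 8300 patients, at least 90% in ZODIAC, at most 20% interested.
- Cohort: 0.90 × 8300 = 7470
- Platform: 0.20 × 7470 = 1494; cohort only: 7470 − 1494 = 5976

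These are built from bounds, with no loss to follow-up. Taking 20% of 8300 instead gives 1660 and 5810.

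**3. Size of the bias.** Bias = f × d, where f is the share of ineligible patients among analysed comparators and d is the shortfall of their 12-month EQ-5D against what baseline predicts. Neither is in the documents; both ranges are assumptions.

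| f | d = 0.05 | d = 0.10 | d = 0.15 |
|---|---|---|---|
| 5% | 0.0025 | 0.0050 | 0.0075 |
| 10% | 0.0050 | 0.0100 | 0.0150 |
| 15% | 0.0075 | 0.0150 | 0.0225 |

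Against the relevant difference: 0.0025/0.074 = 3%, 0.0100/0.074 = 14%, 0.0225/0.074 = 30%. To reach 0.074 at d = 0.15, f would have to be 0.074/0.15 = 49%.

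**4. Against the precision.** With assumed SD 0.20 and baseline-to-follow-up correlation 0.6:

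half-width = 1.96 × 0.20 × √(1 − 0.36) × √(1/1494 + 1/5976) = 1.96 × 0.16 × 0.02893 = 0.0091

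With 1660 and 5810 it is 0.0087. Four of the nine cells exceed 0.0091. If half of each group were lost, the half-width would be 0.0091 × √2 = 0.0128, and three cells would still exceed it.

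**The case against.** **The comparator is not named.** The use/non-use factor stands under the e-VitaDM heading, and the section on determinants of platform use shows that interested patients may turn out not to use the platform. If the contrast were users against non-users within e-VitaDM, both sides would have passed the same criteria. Table 1 is a data schedule, not a definition of the analysis population, and the patient-flow figure was not in the text reviewed. This stands as a limit on certainty. Even so, the two columns of Table 1 and the collection of EQ-5D in patients not interested in the platform make cohort-only patients the more natural reading.

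**Few ineligible patients may reach the analysis.** A reader might infer that all of them enter the comparator. The documents do not support that. Data are used only with consent and completed questionnaires; patients with dementia or little Dutch are among the least likely to supply either, and terminally ill patients will often have no 12-month value. This may make f small, but no rule makes it zero.

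**The interest comparison.** A reader might infer that ineligible patients are counted as uninterested. The Abstract defines those groups by expressed interest, and nothing says how ineligible patients are classified.

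**Other outcomes.** A reader might infer that WHO-5, PAID-5, SDSCA and the clinical measures are all biased towards the platform. Nothing in the documents fixes the direction for these; glycaemic control in a terminally ill or cognitively impaired patient could move either way.

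**Size.** The illustrated bias is at most about a third of the predefined relevant difference. That stands, and it lowers the severity.

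**Conclusion.** The point holds in limited form. As written, five eligibility criteria screen the platform group and not the cohort-only group, and the planned adjustment cannot make up for the missing overlap. On EQ-5D the likely direction favours the platform. The size cannot be derived from the documents; the illustration of 0.0025-0.0225 rests on the assumed f and d, and its comparison with 0.009 on the assumed SD, correlation, group sizes and full follow-up.

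This source alone would not plausibly produce a difference of 0.074. It could produce or inflate a statistically significant difference of no clinical relevance. The finding also depends on cohort-only patients being the comparator, which the article implies but does not state. It should be fixed because the remedy is cheap and hard to apply later; it does not by itself invalidate the study.

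**What to change.** State that the non-users in the e-VitaDM analysis are cohort-only patients, if that is meant. At T0, record the listed e-VitaDM exclusion criteria for every ZODIAC participant, and restrict the use/non-use comparison to patients with none of them. Leave the open-ended investigator criterion out of the comparator flag: it cannot be applied consistently to patients who never sought the platform. A small asymmetry from that criterion remains. Keep the unrestricted cohort for the ZODIAC prognostic analyses, where having no exclusions is reasonable.

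For the recorded criteria this component of bias then becomes zero by construction; self-selection by interest remains.

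The cost is a short checklist, since language ability and interference with participation may not be in GP records, and a somewhat smaller comparator. Losing 15% of 5976 leaves about 5080, and the half-width becomes 1.96 × 0.16 × √(1/1494 + 1/5080) = 0.0092 instead of 0.0091.

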### Setting

The CGD is one of the care groups connected to our Diabetes Centre for benchmarking and study purposes for years. It is the largest care group in The Netherlands, including over 500,000 subjects and over 200 GP’s, divided over 110 practices. 52 out of the 110 general practices agreed to participate in the e-VitaDM/ZODIAC study. In these practices approximately 8300 T2DM patients were treated in 2011.

In line with clinical guidelines, patients in CGD are seen four times a year, of which one visit is the annual check-up. All patients with T2DM fulfilling the inclusion criteria, will be asked to participate in the prospective observational cohort study (ZODIAC) three months before their annual check-up. They are also informed about the possibility to use the care platform (e-VitaDM). Patients who express interest in using the platform are registered on the platform by their primary care nurse (PN) and will be included in the e-VitaDM study. The PN’s are trained to offer their T2DM patients information and guidance with the use of the platform and its educational content. Participants will be able to use the platform after their written consent and registration by their PN.

### Study duration

The inclusion period will last one year and the follow-up period for the e-VitaDM part will last one year and three months. This will result in a study duration of two years and three months. A complete set of data of an individual person (clinical measures and questionnaires) is available at the annual check-up and at one year. Figure 3 shows the individual timeline.

**Figure 3 F3:**
[figure not shown]
Individual timeline.

### Information on interactive care platform

A selection of DM-related health measurements as performed at the annual check-up will be provided on the platform to the individual participant, accompanied with an explanation of each item. These measurements are available from 2009 onwards, so patients will see their results over some years. Results will be displayed textually as well as graphically, showing individual values as well as the development of values over time (see Additional file 1).

Furthermore, educational information will be presented to the participant based on gender, age and actual laboratory results and clinically important measurements (e.g. HbA1c and blood pressure), using pre-programmed algorithms. In this way, a patient specific profile is created to allow a more tailored approach in offering education. After presentation of specific information to the patient, understanding of this information will be tested by a few questions. If patients allow, their care provider will receive an automated message in the electronic patient record, indicating that the participant has completed an educational module. This information can be used as input during the next visit with the GP or PN.

In addition, participants can improve their health by setting goals and actions as part of the self-management module. The development of the self-management module in e-Vita is based on the Health Action Process Approach (HAPA) model of behaviour change and the Proactive Interdisciplinary Self-Management (PRISMA) course [12].

The platform is designed with emphasis on making it suitable and available for all T2DM patients. From the start, special focus groups of caregivers and caretakers are actively involved in designing and testing of this platform.

The platform is reached through an HTTPS-connection and a multi-factor authentication. Development and hosting of the platform is based on NEN-procedure 7510, ISO 27001, Security Access Layer (SAL), Personal Data Protection Act (in Dutch: Wet Bescherming Persoonsgegevens (WBP)) and National Cyber Security Centre’s ICT Security Guidelines for web applications part 1 and 2, in which a code for protection of information is determined.

